## FEASIBILITY AND RECRUITMENT PROCEDURES

Patient recruitment will be carried out by the department caring for patients with PD (Toulouse University Hospital, B8 Neurology Department, Parkinson's Expert Centre (CEP)). During a routine care consultation, the neurologist will check the patient's eligibility criteria and offer to participate in the study. Patients will be re-evaluated in consultation by an investigating physician during the inclusion visit, after signing the informed consent (V1). 1500 patients are currently being monitored at the Toulouse CEP. 2/3 of Parkinson's patients suffer from pain. This active queue should allow us to recruit all patients for this study.

All the research will take place in the Baudot pavilion of the Toulouse Neuroimaging Center (ToNIC – Inserm/UPS UMR1214), which is entirely dedicated to research and located on the site of the Toulouse Purpan University Hospital. PR and MS interventions will be provided in a room dedicated to this purpose and MRIs will be performed within the MRI technical platform.

**7. RESEARCH TREATMENT(S)/STRATEGY(S)/PROCEDURE(S)**

## EXPERIMENTAL TREATMENT/STRATEGY/PROCEDURE

### *Foot reflexology*

The experimental group will receive 4 one-hour PR sessions, spaced 3 weeks apart each.

The FR will be carried out by [name], CNRS researcher, seconded to INSERM, trained and certified in reflexology. The specific PR protocol used in the present study has been designed in collaboration with experienced reflexology practitioners and will be identical for all patients and for all sessions. This protocol stimulates the reflex zones associated with the management of pain, stress and emotions. These sessions are already described.

A reflexology session lasts one hour and takes place in three stages:

- The pre-session dialogue: the practitioner welcomes the patient and collects some information on the patient's bodily feelings and expectations that day. (Ask the patient if there is any particular pain that needs more attention).
- Practice: The patient is comfortably seated in a massage chair, with his legs slightly raised and his feet bare. The practitioner disinfects the patient's feet and then takes them in hand, starting with a few relaxation movements to release tension and allow relaxation. A neutral massage balm will be applied and then, depending on the group, the FR or SM protocol will then be dispensed by the teacher.
- Post-session dialogue: the facilitator collects the person's sensations and feelings as well as

the reflex zones on which he dwelt, if any.

### *Description of the foot reflexology protocol*

- The reflexological massage technique is exclusively manual, it is practiced with the pulp of the thumb and index finger. The pressure of the finger is perpendicular to the surface of the skin, for a few mm, then the finger moves with a rotational pressure movement in search of the reflex zones according to the established protocol. The practitioner may perceive changes in the texture of the skin (indurated, less elastic, presence of granulations) and will emphasize these areas by various appropriate techniques adapted to the patient's feelings: pressure, tissue listening and mobilization.
- The specific reflexology protocol used in the present study was designed in collaboration with experienced reflexology practitioners ([name], certified from the RTTFA school - Martine Faure-Alderson). This protocol stimulates the reflexes associated with Parkinson's disease symptomatology and emotional response:
- Starting with the left foot and then the right foot.
- Full Foot Smoothing x3
- Malleoli Smoothing x3
- Listening to the primary respiratory movement
- Circuit Spine (from the SSB to the coccyx, AR on the inner edge of the foot), starting with the left foot and then the right foot.

[figure not shown]

- 10 points of the brain on the big toe (Starting with the left foot and then the right foot)

[figure not shown]

1. Occipitocervical joint
2. Brainstem, with significant stimulation on the top (locus niger) and on the middle part (raphe nuclei)
3. 4th ventricle and cerebellum
4. SSB, pituitary gland, hypothalamus (basal nucleus of meynert)
5. Cerebellum tent
6. SSB (sphenobasilar symphysis)
7. Sea horse
8. Septum pellucidum
9. Corpus callosum
10. Epiphysis

End of the Spine Circuit to the coccyx then pumping from this point (pressure / relaxation 3x)

- Circuit corresponding to emotional zones
  1. Diaphragm, 9 turns of the foot
  2. Psoas insertion, 3 foot turns

(the psoas and diaphragm insertions being intimately linked)

Insist on the stress axis: 12. adrenal glands + 13. Epiphysis, 14. Hypothalamus and Pituitary Gland: stimulate simultaneously), starting with the left foot and then the right foot.

[figure not shown]

Move up and down the Spine circuit to the tailbone ▪ 7 plexiglass, starting with the left foot and then the right foot.

[figure not shown]

- Listening to the primary respiratory movement
- Complete smoothing of feet and malleoli

## TREATMENT/STRATEGY/COMPARISON PROCEDURE

The control group will receive 4 sessions of SM, feet and calves, of one hour, spaced 3 weeks apart by the same worker. Patients drawn at random from the group that will benefit from the SM will have a foot and calf massage without stimulating the foot reflexology points. This massage will be the same for all patients in this group and for all sessions.

The SM technique is exclusively manual, it is practiced with the hands. The pressure of the hands is perpendicular to the surface of the skin, for a few mm, and move according to the established protocol:

- Full Straightening (Foot + Calf) x3
- Malleoli Smoothing x3
- Full Calf Smoothing x3
- Inner kneading of the calf
- External kneading with the palm
- Friction
- Calf straightening x3
- Soft knee straightening
- Knee side smoothing x3
- Full Smoothing
- Heel straightening
- Pumping the hollow of the foot
- Arch pressure
- Foot smoothing
- Stress of the metatarsals
- Rotation and light toe stretching
- Foot Smoothing x3
- Smoothing between metatarsals
- Ankle Smoothing x3
- Soft-Sided Cat Paste

The content of the sessions, PR and MS, has been standardized, in order to guarantee the reproducibility of the study and its transfer to clinical practice.

**8. PROCESSING AND ASSOCIATED PROCEDURES**

## ASSOCIATED TREATMENTS/PROCEDURES ALLOWED

### Ancillary Medications

All anti-Parkinson's treatments will be taken according to the neurologist's prescription.

They will not be altered by their participation in the study.

They should be stable throughout the duration of the study and at least for 4 weeks before the initiation of the FR or SM sessions.

### Other treatments/procedures

Analgesic drugs are also authorized regardless of their pharmacological class. We will thus be able to observe the variation in the consumption of these analgesic drugs during the study. A treatment collection booklet will be provided to the patient.

## PROHIBITED ASSOCIATED TREATMENTS/PROCEDURES

All massages or reflexology sessions, outside the research program, are prohibited. During the week preceding the inclusion visit (V1) and throughout the duration of the study, all non-drug interventions are prohibited (osteopathy, acupuncture, etc.).

**9. CONDUCT OF THE RESEARCH**

## RESEARCH TIMELINE

- Length of Inclusion Period: 2 years
- Duration of participation of each participant: 12 weeks - Total duration of the research: 2 years and 3 months

## SUMMARY TABLE OF PARTICIPANT MONITORING

| 4 FR vs SM sessions every 3 weeks +/- 3 days | | | | |  | |
| --- | --- | --- | --- | --- | --- | --- |
|  | In consultation | V1 | V2 (3S) | V3 (6S) | V4 (9S) | V5 (12S) |
| Eligibility | ✓ | ✓ |  |  |  |  |
| Informed Consent (R) |  | ✓ |  |  |  |  |
| RP or MS (R) |  | ✓ | ✓ | ✓ | ✓ |  |
| EVA (S) | ✓ | ✓ | ✓ | ✓ | ✓ | ✓ |
| KPPS (R) |  | ✓ |  |  |  | ✓ |
| BPI (R) |  | ✓ |  |  |  | ✓ |
| Mac Gill (R) |  | ✓ |  |  |  | ✓ |
| CPAQ-8 (R) |  | ✓ |  |  |  | ✓ |
| 3 PDQ (R) |  | ✓ |  |  |  | ✓ |
| TCI |  | ✓ |  |  |  |  |
| Thermotest (R) |  | ✓^^[[1]](#footnote-1)^^ |  |  | ✓1 |  |
| Tolerance to Heat |  | ✓1 |  |  | ✓1 | ✓ |
| MDS UPRDS III (S) |  | ✓ |  |  |  | ✓ |
| HAD (R) |  | ✓ |  |  |  | ✓ |
| fMRI (R) |  | ✓ |  |  |  | ✓ |
| Adverse Event Collection |  | ✓ | ✓ | ✓ | ✓ | ✓ |

## PRE-INCLUSION TOUR

### Itinerary of the visit

The pre-inclusion/inclusion visit is carried out by the investigating doctor. The pre-inclusion visit takes place between 2 months and no later than 1 week before the inclusion visit. During the pre-inclusion visit, the investigating physician informs the participant and answers all questions about the objective, the nature of the constraints, the foreseeable risks and the expected benefits of the research. It also specifies the rights of the participant in the context of a search and verifies the eligibility criteria.

The pre-inclusion visit is a routine care consultation where the investigating physician verifies the patient's eligibility to participate in the study. He evaluates the patient's pain and offers him research.

A copy of the information note and consent form is then given to the participant by the investigating physician. After this information session, the participant has a period of reflection. The patient informs us of his decision by phone. If he agrees, his schedule is scheduled.

## INCLUSION VISIT / RANDOMIZATION PROCESS

### Collection of consent

Prior to any research-related review, the investigator obtains the free, informed, and written consent of the participant (or his/her legal representative if applicable).

If the participant gives his or her consent to participate, the participant and the investigator write their first and last names in plain text, date and sign the consent form. This must be signed BEFORE CARRYING OUT ANY CLINICAL OR PARACLINICAL EXAMINATION REQUIRED BY THE

RESEARCH. The consent is signed in 2 copies, one of which is delivered to him in person.

Once eligibility has been verified and consent has been signed, randomization can take place. When an investigator wishes to perform randomization after verifying the participant's eligibility, they log on to the website: http:// XX . The investigator completes the "randomization" web page after having previously confirmed all the patient's eligibility criteria on the site. After validation of the content, randomization is performed and the site immediately communicates to the investigator the unique number of the participant in the research, the result of the randomization, in particular the procedure group allocated to the patient.

Following randomization, each participant will benefit from an evaluation at inclusion:

- **Socio-demographic data (age, sex).**
- **PD treatments, analgesic treatments and concomitant treatments in progress.**
- **Pain that includes:**
  - The maximum and average VAS over the previous week *[Price 1994]*
  - The KPPS: a scale that assesses the intensity of pain in PD *[Chaudhuri 2015]*
  - The BPI *[Brasseur 1997]* - The Mac Gill *[Turk 1985]*
  - CPAQ-8: a questionnaire that assesses the extent to which the person "accepts" the presence of pain *[McCracken 2004]*
  - 3 PDQ (Parkinson's Primary Pain Questionnaire)
- **Motor state, anxiety and depression which include:** - The MDS UPRDS III scale *[Defebvre 2018]*

- HAD (Hospital Anxiety and Depression) scale *[Lépine 1985]*

- **the intensity of the pain thanks to the VAS before each FR vs SM session (from V1 to V4) over the last 7 days,**
- **an assessment of the subjective pain perception threshold and heat tolerance via the thermotest before and after the FR vs SM session**
- **An assessment of the personality profile using the TCI personality questionnaire.**

The 15 patients in each group will benefit from an fMRI before the first session of FR vs SM at the Baudot technical platform.

**Following all these evaluations, the patient will benefit from the 1st session of PR, or MS, performed by the reflexologist.**

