## JUSTIFICATION OF METHODOLOGICAL CHOICES

Critics of non-drug interventions and FR claim that the effect is only placebo or related to management and patient/therapist interaction. This is why, in the present study, we propose to study the impact of FR management compared to a sham massage (SM), with the same reflexologist practitioner, in order to avoid a bias related to the personality of the therapist and therefore to the patient's care.

In addition, the patient will be informed that he or she will be randomly selected to benefit from an analgesic NPI, explaining that two different techniques are being studied in this protocol. The patient will thus be blinded.

In order to ensure objective evaluation and blinded data analysis, the person in charge of pain assessment of Parkinson's patients will not be informed of the patient's randomization. This is why we talk about double-blind in this study.

The rigorous evaluation of pain in this study led us to select many questionnaires that evaluate the different aspects of pain. This will allow us to cross-reference the different information in order to strengthen the observation of the impact of the management of FR.

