**4. JUDGING CRITERIA**

### 4. PRIMARY OUTCOME

The primary outcome of this study is the variation in mean pain intensity during the previous week, rated on an VAS (from 0 = no pain to 10 = maximum imaginable pain), before and after management between the 2 groups of patients (FR vs SM). Pain intensity on VAS is a validated clinical criterion for the global assessment of the discriminative and emotional aspects of pain *[Price 1994].*

We chose to assess the intensity of the overall pain and not the intensity of the different types of pain. Indeed, we believe that this type of intervention can have a non-specific effect on pain and therefore reduce the perception of pain in general and thus improve the daily life of patients. The variation corresponds to the raw delta between the VAS score at baseline (V1) and that after the 4 sessions of FR vs SM at the last visit (V5).

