**5. RESEARCH DESIGN**

## RESEARCH OUTLINE

Due to the lack of published data on the subject, it was chosen to conduct a pilot study, since FR has not yet been evaluated in a population of Parkinson's patients in order to reduce their chronic pain.

It is therefore a single-center, longitudinal, prospective, double-blind, randomized exploratory study in 2 parallel groups (1:1 ratio): 1 group benefiting from FR sessions, 1 control group benefiting from foot MS sessions. Both the patient and the pain assessor will be blinded.

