## METHODS FOR RANDOMIZATION

Patients will be randomized into two groups in a 1:1 ratio, the experimental group that will receive the FR sessions and the control group that will receive the foot SM.

Randomization will be established by the MeDatas cell of the Clinical Investigation Center (CIC). When a subject is included, the assignment of a number and group will be established by means of a secure randomization interface via the CIC website.

Subjects will be randomized once the investigator verifies that they meet the eligibility criteria (Section 5). Patients will be randomized to one of 2 groups according to the chronological order of inclusion of patients in the protocol.

Randomization will be done at the inclusion visit. Only the person in charge of foot reflexology and sham massages ([name]) will be informed of the patient's randomization.

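### The protocol contradicts itself on who learns the allocation: one section restricts it to the practitioner, another sends it to the investigator before the V1 baseline, including the primary-outcome VAS, is recorded

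*Protocol*

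**What the plan says.** Section 5, Methods for Randomization, sets the rule. "Only the person in charge of foot reflexology and sham massages" is to be told the result.

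Section 9, Inclusion Visit / Randomization Process (Collection of consent), describes the procedure. The investigator logs on to the randomisation site, confirms eligibility and randomises, and then "the site immediately communicates to the investigator the unique number of the participant in the research, the result of the randomization". The sentence goes on to make plain that this covers the arm itself: "in particular the procedure group allocated to the patient".

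The same text fixes the order of events: "Following randomization, each participant will benefit from an evaluation at inclusion". The list that follows includes "The maximum and average VAS over the previous week", KPPS, BPI, McGill, CPAQ-8, 3PDQ, MDS-UPDRS III, HAD, the thermotest and the TCI. A pre-session fMRI is added, and the first session comes after all of these.

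Section 4, Primary Outcome, makes the V1 score the starting point: "The variation corresponds to the raw delta between the VAS score at baseline (V1) and that after the 4 sessions of FR vs SM".

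On blinding, section 5 (Research Outline) states that "Both the patient and the pain assessor will be blinded". Section 2 (Justification of Methodological Choices) states that "the person in charge of pain assessment of Parkinson's patients will not be informed of the patient's randomization". Section 9 (End-of-Research Visit) gives the pain assessment to a blinded clinical research associate. Section 9 (Pre-Inclusion Tour) has the investigating doctor carry out the inclusion visit.

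**The concern.** The trial exists to separate a specific effect of reflexology from placebo and from contact with the therapist, so blinding carries much of its weight. The practitioner cannot be blinded. The investigator can be, and section 5 intends this. A site that follows section 9 literally breaks section 5 for every patient, and no analysis can repair that afterwards.

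The sequence adds to the problem. The V1 VAS is one of the two measurements in the primary endpoint, and it also enters the responder definition and the visit-by-visit deltas. It is recorded after the group has been disclosed to someone with a role in the same visit. If that knowledge affected how baseline pain was elicited or recorded in one arm, the resulting difference would look like a treatment effect.

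**Working it through.** The protocol gives no figure for this point. The check compares the texts and then works through an illustration.

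**Step 1: who may know and who is told.**
- Rule (section 5): only the practitioner.
- Procedure (section 9): the investigator, and what is sent is the group itself, not just a number.
- Related text (section 14, Data Management): unblinding follows the data freeze. Under the section 9 procedure the investigator would already know the group from V1.

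No other section reconciles the rule with the procedure.

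**Step 2: order of events at V1.** Section 9 gives consent and eligibility, randomisation with disclosure to the investigator, baseline scales and fMRI, then the first session. The V1 VAS therefore follows disclosure. A VAS is also taken at the earlier consultation, but the primary delta does not use it.

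**Step 3: who rates at V1.** The blinded research associate is named only under the End-of-Research Visit. The inclusion-visit text names no assessor, and the investigating doctor carries out the visit. MDS-UPDRS III is scored by an examiner and the KPPS is worded for a rater, so not everything at V1 is self-report.

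**Step 4: a second disclosure route.** Section 13 (Data Privacy) builds the participant code partly from the group number. Section 14 puts the pseudonymised code in the report book, and section 13 (Source Data) has rating scales entered directly into the CRF. An assessor who is never told the allocation would still handle a code that carries it.

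**Step 5: how a shift would carry through.** Let D = V5 - V1. If V1 in one arm is recorded b points too high, then D* = V5 - (V1 + b) = D - b, and the between-arm difference moves by exactly b. Section 11 plans a Wilcoxon Mann-Whitney test on the raw deltas with no baseline adjustment, so nothing absorbs b.

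**Step 6: illustration of size.**
- Patients per arm: 15 planned. With the 25% departures in section 11, 15 x 0.75 = 11.25, taken as 11.
- SD of change: not in the protocol. Section 11 gives 1.5 for the VAS itself. With equal SDs at both visits, SD(D) = 1.5 x sqrt(2(1 - r)), where r is the V1-V5 correlation. This is 1.5 at r = 0.5 and 2.12 at r = 0.
- Shift b: an assumption, shown at 0.25 and 0.5 points.
- Test: two-sided t-test at 0.05 as an approximation to the planned rank test, with noncentrality (b/SD) x sqrt(n/2) and 2n - 2 degrees of freedom. For example, b = 0.5, SD = 1.5, n = 15 gives 0.333 x 2.739 = 0.913.

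Rejection probability when there is no true effect:

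| Shift b | SD of change | n = 11 | n = 15 |
| --- | --- | --- | --- |
| 0.25 | 1.5 | 6.6% | 7.3% |
| 0.25 | 2.12 | 5.8% | 6.1% |
| 0.5 | 1.5 | 11.6% | 14.3% |
| 0.5 | 2.12 | 8.2% | 9.6% |

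A 0.5-point shift is a quarter of the 20 mm (2-point) difference in section 11.

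**The case against.** The strongest reply is that disclosure goes to the investigator, not to the patient or the pain assessor. The VAS is the patient's own rating, and the protocol says several times that patient and assessor are blinded. The sentence naming the research associate follows one about comparing pain at each visit throughout the study, so it can be read as covering V1. On that reading, V1 is biased only if the informed investigator takes part in a rating given to others, or influences it. This stands as a limit on the consequence. It does not remove the contradiction, and it leaves the V1 assessor unnamed in a visit carried out by the investigating doctor.

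Section 9 still has a placeholder web address and the protocol was built on a model document, so the disclosure sentence may be unedited template wording. That is plausible but cannot be shown, and it is the operative text.

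Once the investigator no longer receives the group, a post-randomisation baseline carries little of this risk. That also stands, and it makes reordering V1 secondary.

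Three stronger readings are tempting, and the protocol does not support them:
- **The unblinded investigator controls who leaves the trial.** The stopping rules in section 9 include modified anti-parkinsonian treatment and major deviation, but they name nobody who applies them. The first rule listed is the participant's own withdrawal.
- **Allocation concealment fails.** Randomisation follows consent and eligibility, so the disclosure comes after the decision to include.
- **The false-positive rate is 12-14%.** That is one scenario, with a 0.5-point shift, an SD of change of 1.5 and a t-test. The protocol gives neither the shift nor that SD, and it plans a different test.

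**Conclusion.** The contradiction between sections 5 and 9 is certain from the text and needs correcting. It is also certain that section 9 places the V1 evaluation, including the baseline of the primary delta, after the group has been sent to the investigator. Bias in the V1 VAS is a risk that the text leaves open, not a demonstrated effect, because patient and assessor are meant to be blinded and the gap is an unnamed V1 assessor. If a baseline shift occurred it would enter the treatment contrast in full. The false-positive rate would be about 6-7% for 0.25 points and about 8-14% for 0.5 points, against a nominal 5%, under the assumptions stated in the illustration. The case for amendment rests on the contradiction, not on those percentages.

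**What to change.** 1. Amend section 9 so that the randomisation site returns only the participant number to the investigator and sends the allocated group only to the practitioner, as section 5 states. In section 13 (Data Privacy), remove the group number, and the order of inclusion within group, from the participant code. The cost is a recipient setting on the site, a new numbering rule and two edited paragraphs.

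2. As a further safeguard, do one of the following:
   - Complete the pre-session V1 assessments and the fMRI after consent and eligibility, and randomise immediately before the first session. Visit and assessments are unchanged. The small downside is that a few patients may complete baseline and not be randomised.
   - Keep the present order and state in the inclusion-visit text that the blinded research associate collects the V1 scales.

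Neither step adds visits, patients or measurements.
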